### 2.3. Sample Size Calculation

The present study is not powered for any confirmatory inference. The targeted roster sizes (approximately 15–25 athletes per team) are sufficient to evaluate feasibility and engagement and to provide preliminary clustering estimates (i.e., intraclass correlation coefficient). We will report these estimates with 95% confidence intervals. Precision will be limited by the small number of teams. Published intraclass correlation coefficient (ICC) values will also inform power for a future cluster-randomized trial.

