### 2.4. Procedure

Coaches and high school student-athletes will be recruited from a purposive sample of two public high schools within a district that reflects a diverse demographic composition. Schools will serve as the unit of randomization and will be randomly assigned to either the TN intervention group or the waitlist control group. Four weeks prior to the start of the season, head coaches will be contacted via email, using the contact information provided by the district athletic director. Following pre-screening to confirm their coaching role, coaches will be invited to complete an online enrollment survey that includes the purpose of the study, its procedures, and an option to opt out. Coaches who consent to participate will be listed under the intervention or control condition. Two teams from each school will then be randomly selected for inclusion, resulting in a total of four participating teams. To prevent potential contamination, both teams from the same school will remain in the same condition, consistent with school-level group assignment. Teams in the intervention group will have access to TN throughout the season, whereas teams in the control group will serve as a waitlist control and receive access after the study is completed.

Parental consent and student-athlete assent will follow IRB-approved procedures appropriate for research with minors. Given that the study involves a non-clinical, educational mobile platform and poses no greater than minimal risk, the research team will seek for a passive (opt-out) parental consent process, consistent with school district research policies.

Parents or legal guardians will receive an informational letter via email two weeks before data collection, describing the study purpose, procedures, confidentiality protections, and voluntary nature of participation. The letter will include both an online opt-out form and contact information for the research team. Those who do not opt out will be considered to have provided consent. Student-athletes will then provide electronic assents prior to participation, with the option to withdraw at any time without penalty.

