### 2.9. Data Analysis

Analyses will use linear mixed-effects models (LMMs) estimated via REML to account for nesting (student-athletes within teams within schools) and to accommodate unbalanced repeated measures. Fixed effects will include condition (intervention vs. waitlist control), time (baseline, mid-, and end-season), and their interaction; random intercepts will be specified for team and school. Missing data will be handled by maximum-likelihood under MAR; if attrition exceeds 20%, multiple imputation will be used as a sensitivity analysis. Prespecified covariates include type of sport, gender, grade, and prior mental-health support. Given the pilot nature and very limited clusters, results will emphasize descriptive effect sizes with 95% CIs and ICCs/design effects rather than confirmatory *p*-values; where *p*-values are reported, we will control the false discovery rate (Benjamini–Hochberg) across outcomes.

Because cluster-randomized designs with few clusters are susceptible to chance baseline imbalances, baseline values of each outcome will be included as covariates in all longitudinal models. This baseline-adjusted specification is expected to improve precision and reduce bias attributable to baseline differences between conditions. As a sensitivity analysis, estimates will be examined with and without adjustment for multiple comparisons to evaluate the robustness of observed patterns. These analyses are intended to support transparent interpretation of exploratory findings.

Verbatim transcriptions of coach and student-athlete interviews will be analyzed using rapid content analysis to identify key usability insights, perceived benefits, and improvement opportunities related to the TN platform. The analysis will prioritize efficiency and practical relevance in studies with small samples, maintaining analytic rigor through structured coding and documentation. Two researchers will independently review transcripts, generate preliminary codes, and summarize key points within a shared matrix. Codes will then be grouped into higher-order categories to capture salient patterns in user experience and acceptability ([Bibr B6-behavsci-16-00268]). Findings will be summarized thematically but interpreted as exploratory, descriptive feedback rather than claims of thematic saturation. NVivo 12 ([Bibr B31-behavsci-16-00268]) will be used for data organization and coding.

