## 4. Expected Results

We expect to observe trends consistent with potential benefits of TN (e.g., improved satisfaction, motivation, and well-being; reduced burnout), alongside feasibility metrics (adherence, engagement, data completeness). Estimated ICCs and design effects will guide sample-size planning for a fully powered cluster-randomized trial.

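### The only model described for the ICCs adjusts for baseline and also counts baseline as an outcome wave, so planning ICCs taken from it would be too low for some uses in sizing the next trial

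*Protocol article*

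**What the plan says.** Section 2.9 specifies linear mixed models with fixed effects for condition, "time (baseline, mid-, and end-season), and their interaction; random intercepts will be specified for team and school". A later paragraph of the same section adds that "baseline values of each outcome will be included as covariates in all longitudinal models". Reporting is to centre on "descriptive effect sizes with 95% CIs and ICCs/design effects".

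Section 4 gives these figures a purpose: "Estimated ICCs and design effects will guide sample-size planning for a fully powered cluster-randomized trial". Section 2.3 describes the ICC as a preliminary clustering estimate with a 95% confidence interval, concedes limited precision, and adds a second source: "Published intraclass correlation coefficient (ICC) values will also inform power for a future cluster-randomized trial".

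The article does not say whether the reported ICC is conditional on baseline or unconditional, nor which SD belongs with it.

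**The concern.** An athlete's baseline score carries whatever persistent effect the team has. Adjusting for it therefore removes part of the between-team variance that an ICC is meant to describe. That is legitimate for estimating a treatment effect, but the ICC left over answers a different question from the unadjusted ICC.

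The specification adds a second problem. Baseline is both a time level, hence an outcome row, and a covariate for that same row. The baseline rows then have almost no residual variance, which pulls down both the team variance and the total variance.

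Producing planning figures is one of the pilot's main uses. A confidence interval shows that an ICC is imprecise. It does not show that the ICC measures something other than what the next trial's sample-size formula needs.

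**Working it through.** The article states no ICC, design effect or sample size to reproduce, so the check runs on labelled assumptions.

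**Inputs**
- From the documents: 15 to 25 athletes per team (section 2.3; midpoint m = 20 used), four teams in two schools (section 2.4), three waves and baseline as covariate (section 2.9).
- Assumed: total variance 1 at each wave; true team ICC 0.05; within-athlete correlation r = 0.5 to 0.7; correlation π of team effects across waves = 1, 0.8 or 0.5. School variance is set aside: with one school per arm it cannot be separated from condition.

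**1. Reference.** Unadjusted design effect = 1 + 19 × 0.05 = 1.95.

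**2. The model as written (three rows, team intercept).** Pooling the rows, the baseline slope is b = (1 + 2r)/3. At r = 0.6, b = 0.733. Within-team residual variances are:
- baseline row: (1 − b)² = 0.071
- follow-up row: 1 + b² − 2br = 0.658

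Their average over three rows is 0.462.

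For a team's mean residual over the rows, let g(c) = (1/3 − b)² + (2 + 2c)/9 + 2(1/3 − b)(2c/3). At r = 0.6, g(1) = 0.0711 and g(0.6) = 0.1956. With π = 1:
- variance of the team mean = 0.05 × 0.0711 + 0.95 × 0.1956/20 = 0.01285
- total residual variance = 0.05 × 0.0711 + 0.95 × 0.4622 = 0.4427
- within-team mean square = (0.4427 − 0.01285) × 60/59 = 0.4371
- team variance = 0.01285 − 0.4371/60 = 0.00556
- ICC = 0.00556/0.4427 = 0.0126; design effect = 1 + 19 × 0.0126 = 1.24

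**3. The standard adjusted model (one follow-up, baseline as covariate only).** Team variance = 0.05(1 + r² − 2rπ); athlete variance = 0.95(1 − r²). At r = 0.6, π = 1: 0.008 and 0.608, total 0.616, ICC 0.013, design effect 1.247.

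**4. Size of the next trial.** The required number is proportional to variance × design effect. Two misuses are shown:
- (a) the as-written design effect with a raw SD, next trial analysed without baseline adjustment: shortfall = 1 − DE/1.95;
- (b) the as-written ICC with its own residual SD, next trial analysed with baseline adjustment: shortfall against the pair in step 3. At r = 0.6, π = 1 this is 1 − (0.4427 × 1.239)/(0.616 × 1.247) = 1 − 0.548/0.768 = 29%.

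| π | r | ICC as written | Design effect | Standard adjusted ICC | Shortfall (a) | Shortfall (b) |
|---|---|---|---|---|---|---|
| 1.0 | 0.5 | 0.014 | 1.26 | 0.017 | 35% | 30% |
| 1.0 | 0.6 | 0.013 | 1.24 | 0.013 | 36% | 29% |
| 1.0 | 0.7 | 0.011 | 1.22 | 0.009 | 38% | 27% |
| 0.8 | 0.5 | 0.017 | 1.33 | 0.031 | 32% | 38% |
| 0.8 | 0.6 | 0.019 | 1.36 | 0.032 | 30% | 39% |
| 0.8 | 0.7 | 0.022 | 1.42 | 0.037 | 27% | 41% |
| 0.5 | 0.5 | 0.023 | 1.43 | 0.050 | 27% | 46% |
| 0.5 | 0.6 | 0.028 | 1.53 | 0.059 | 21% | 48% |
| 0.5 | 0.7 | 0.037 | 1.70 | 0.075 | 13% | 51% |

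REML fits to 800 simulated teams of 20 agree within sampling error: 0.008 to 0.012 at π = 1, 0.017 to 0.025 at 0.8, and 0.021 to 0.038 at 0.5.

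**5. Where no undersizing arises.** Pair the standard adjusted design effect with a raw SD for a baseline-adjusted trial. The number obtained is 1/(adjusted variance) times the number needed, which is 1.33 to 2.05 over the nine cases. As an example, take an assumed effect of 0.3 SD, two-sided 5%, 80% power: 175 per arm before inflation, hence 342 with ICC 0.05 and 209 with ICC 0.01. Those 209 give about 59% power in an unadjusted analysis. In a baseline-adjusted one (r = 0.6) they give about 94% (π = 1) or 86% (π = 0.8).

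**6. Precision.** For an estimate of 0.05 from four teams of 20, the exact 95% interval is about −0.02 to 0.58 on 3 degrees of freedom. The upper limit is 0.80 on 2, once condition is fitted. With a true ICC of 0.05 and no baseline adjustment, 37% to 44% of such pilots would still show 0.01 or less.

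**The case against.** **The source of the ICC is left open.** The article never names the model that supplies the ICC, and a condensed article may leave this to a fuller plan. It is true that the link is an inference. It rests on the word all in the covariate rule and on there being no other outcome model in the text. What is criticised is that rule combined with the three-level time factor, both of which are stated.

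**A conditional ICC can be the right one.** A successor trial analysed with baseline adjustment should use the adjusted ICC with the adjusted SD. This stands for a standard adjusted ICC, and step 5 shows that even a raw SD is then safe. It does not rescue the as-written figures, because the baseline rows shrink their SD as well.

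**The fall to 0.01 is close to an extreme.** It needs fully stable team effects. At π = 0.5 the standard adjusted ICC does not fall at all and may rise. This stands, and the range is reported for that reason.

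**Imprecision is larger and already disclosed, and published ICCs will also be used.** Both are true. Neither tells a reader which version of the ICC is being reported or compared.

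A reader might infer that the next trial will be far too small whatever is done. The documents do not support that: they plan no particular analysis or SD for it, and the outcome depends on both. A reader might also infer that a further baseline discount on a raw-SD sample size counts the gain twice. At r = 0.6, π = 1 it does not: 175 × 0.64 × 1.247 is about 140 per arm, against 175 × 0.768, about 134 needed.

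**Conclusion.** The concern holds in a limited form. If the planning ICC is taken from the only model described, an assumed true 0.05 appears as roughly 0.01 to 0.04, depending on how stable team effects are, with a design effect of about 1.2 to 1.7 against 1.95.

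The shortfall is 13% to 38% if the figure is used with a raw SD for a trial analysed without baseline adjustment. It is 27% to 51% if the as-written ICC and its own SD are used together for a baseline-adjusted trial. A standard baseline-adjusted ICC used with a raw SD for a baseline-adjusted trial was not undersized in any case computed.

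All of this assumes 20 athletes per team and r of 0.5 to 0.7, and it sits beside a larger uncertainty from having four teams. It deserves correction because the ICC is a stated product of the pilot and the remedy is cheap.

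**What to change.** In section 2.9:
- Estimate the planning ICC from a separate model without baseline or other covariates, with team and athlete random intercepts and fixed condition and time, or separately at each wave. The athlete intercept matters: in simulation, an unadjusted three-wave model without it overshot a true 0.05, giving 0.055 to 0.072 over r = 0.4 to 0.7 and π = 0.8 or 1.
- Estimate any baseline-adjusted ICC from post-baseline rows only.
- Report both, labelled, each with its 95% confidence interval and matching SD.
- State that published ICCs will be compared with the matching version, and that the next trial will be sized from the version that fits its own analysis.

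The cost is one extra model per outcome, some additional table columns, and a planning figure that will usually look less favourable. It does not cure the imprecision from four teams.

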## 3. Limitations

As a pilot feasibility study with a small number of clusters, this investigation has several important limitations that shape how its findings should be interpreted. Most notably, all quantitative inferences are intended to be interpreted as exploratory assessments of outcome trends rather than as confirmatory evidence of intervention effects. This study has several limitations that should be acknowledged. First, the sample size is modest and limited to two high schools. It limits the external validity of the findings to student-athletes from other geographic locations, educational environment, socioeconomic contexts, or athletic settings. With only two clusters, any between-arm statistical inference is fragile and at risk of inflated Type I error if clustering is ignored; our LMM framework and emphasis on estimation mitigate (but cannot eliminate) this concern. Second, randomization occurs at the team level within each school, which reduces contamination between intervention and control groups but also limits the number of independent clusters. This may reduce statistical power and increase the potential influence of team-level dynamics. Third, the reliance on self-report questionnaires introduces the possibility of response bias, particularly in domains such as stress and well-being, where student-athletes may under- or over-report depending on social desirability. While anonymity will be emphasized, the school-based setting may still affect the candor of responses. Furthermore, adherence is expected to vary, resulting in differing exposure that may attenuate group-level effects. Engagement with TN depends on having reliable smartphone access, data connectivity, and a willingness to use the app throughout the season. In under-resourced communities and populations, limited device availability, shared phones, or constrained data plans may reduce access and engagement, and introduce selection bias. To address this limitation, intervention usage will be objectively monitored via backend usage logs (e.g., logins, completed simulations, time per session, and engagement frequency across the season). Qualitative interview data from coaches and student-athletes will further contextualize usage variability by identifying perceived barriers, facilitators, and reasons for (dis)engagement. Polit data will support the design of future trials.

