## Abstract

Playing sports remains one of the most common avenues for youth engagement in physical activity. Yet mental health challenges, such as performance anxiety, depressive symptoms, reduced motivation, and burnout, place many young athletes at risk. As key mediators of sport participation, coaches’ roles are often underscored in recognizing shifts in athlete motivation, behavior, or well-being. Gaining better insight into athlete mental health status may enable coaches to provide timely support and strengthen athlete and team well-being. In this study protocol, we employ a mixed-methods design, evaluating the effectiveness of an AI-augmented mobile application (i.e., ThriveNudge) in promoting the mental health of youth athletes. ThriveNudge helps coaches monitor athlete mental health, flag mood disruptions, and practice supportive communication via simulated chats. A target sample of four interscholastic teams (with athletes aged 14–18 years) and their head coaches will be recruited. Teams will be cluster-randomized to either the intervention condition (*n* = 2), receiving pre-season training to implement ThriveNudge, or to a waitlist control condition (*n* = 2). Primary outcomes, including athlete burnout, motivation, coach–athlete relationships, and sport enjoyment, will be measured using psychometric scales administered online. Semi-structured interviews will be conducted with coaches and athletes in the experimental group to collect qualitative data on user interface and user experience. We hypothesize that teams using ThriveNudge will report lower athlete anxiety and burnout, higher intrinsic motivation and enjoyment, and stronger coach–athlete relationships than athletes in control teams. We aim to provide a scalable and accessible digital platform that safeguards youth mental health.

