## 2. Materials and Methods

### 2.1. Setting and Design

This study will be conducted in collaboration with two high schools in North America, with data collected from two interscholastic teams at each high school. Two selected high schools will be randomly assigned to either the intervention group, which will use TN, or to a waitlist control group, which will not receive the intervention during the study period. Both groups will follow the rules set by their state’s interscholastic governing body and have access to standard school resources. Coaches will be recruited and informed consent will be obtained prior to student-athlete recruitment. Then, their athletes will be recruited accordingly. Informed consent will be obtained from parents or legal guardians before student-athlete recruitment, and assent will be obtained from all student-athletes. The interventional effect will be evaluated using a quasi-experimental design, and student-athlete outcomes will be measured at the beginning, midpoint, and end of the sport season. To gain an understanding of the experience of using TN, a subgroup of coaches and student-athletes will be recruited for interviews with open-ended questions. Altogether, we will analyze the qualitative and quantitative data using statistical and thematic analyses accordingly. While no monetary incentives will be provided, coaches and student-athletes will be invited to a brief end-of-season presentation where the research team will share key findings and practical takeaways. Participants will also receive a printed brochure with evidence-informed, actionable strategies and resources on mental health and team well-being. This protocol has been preregistered on the Open Science Framework (Registration DOI: 10.17605/OSF.IO/85S9G).

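### With one school per arm, condition and school are the same variable: the planned school intercept and a school-level ICC cannot be estimated, and the mixed model gives no protection at school level

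*Protocol article*

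**What the plan says.** **Unit of randomisation.** Section 2.1: "Two selected high schools will be randomly assigned to either the intervention group", or to the waitlist. Section 2.4: "Schools will serve as the unit of randomization and will be randomly assigned to either the TN intervention group or the waitlist control group". Section 2.4 also keeps both teams of a school in one condition and lets a replacement team inherit its school's condition. Two other places differ. The Abstract has "Teams will be cluster-randomized to either the intervention condition", and Section 3 has "randomization occurs at the team level within each school".

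**Model.** Section 2.9 fits linear mixed models by REML with condition, time and their interaction as fixed effects, and "random intercepts will be specified for team and school". Baseline values are added as covariates. The emphasised outputs are effect sizes with 95% CIs, ICCs and design effects.

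**Use of the clustering estimates.** Section 2.3 calls the roster sizes "sufficient to evaluate feasibility and engagement and to provide preliminary clustering estimates" and adds that published ICCs will also inform the next trial. Section 4: "Estimated ICCs and design effects will guide sample-size planning for a fully powered cluster-randomized trial".

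**Limitation.** Section 3 acknowledges two clusters and a risk of inflated Type I error if clustering is ignored, then states that "our LMM framework and emphasis on estimation mitigate (but cannot eliminate) this concern".

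**The concern.** A random school intercept is meant to widen the between-arm interval by the amount that schools differ from one another. That amount can be estimated only from schools that share a condition, and here no two do. The planned term therefore cannot do its job, and what the software reports for it is arbitrary.

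Two stated outputs are affected: the CI for a between-arm difference in level, and any ICC at the level that was randomised. The text makes the problem harder to see. Section 3 credits the model with partial protection, and nowhere does the protocol say that school and intervention are inseparable. Section 3's description of team randomisation within each school would, if true, remove the confounding, so a reader relying on it would think the intervention effect can be separated from the school.

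**Working it through.** The protocol states no figure to reproduce, so the check is of identifiability and then of size.

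**Inputs from the protocol.** 2 schools, 1 per arm (2.1, 2.4); 2 teams per school, 4 in all (2.4); 15–25 athletes per team, 20 used here (2.3); 3 time points, REML, fixed condition × time, random team and school intercepts (2.9).

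**Assumed, because the protocol gives no values.** School ICC 0.01, 0.03, 0.05; team ICC 0.02–0.10; total variance 1.

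**1. Aliasing.** The fixed-effect matrix (intercept, condition, two time terms, two interactions) has rank 6. With the school indicators added, the rank is still 6. Degrees of freedom for between-school variance are 2 schools − 2 arms = 0. Baseline or other covariates cannot change this, because the school indicators already lie in the span of intercept and condition.

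**2. REML likelihood.** On one simulated data set of this layout, with the other variances held fixed:

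| School variance | REML log-likelihood | SE, condition | SE, condition × end of season |
|---|---|---|---|
| 0 | −76.44492607 | 0.287 | 0.2214 |
| 0.05 | −76.44492607 | 0.427 | 0.2214 |
| 0.5 | −76.44492607 | 1.040 | 0.2214 |
| 5 | −76.44492607 | 3.175 | 0.2214 |

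The likelihood does not move. The condition estimate stays at 0.2691, while its SE follows sqrt(0.2872² + 2 × school variance); at 5 this is sqrt(0.0825 + 10) = 3.175. In three REML fits with statsmodels the school variance stayed at 1.0 each time, with an SE of NaN or about 3 × 10⁷.

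The last column shows that a school intercept cancels from change, so the condition-by-time interval is computable. It contains no team-by-time or school-by-time variance, because the model has none.

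**3. Coverage for a level difference if school variance is set to zero.** With 40 athletes per arm and the team variance treated as known:

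- variance used: V₀ = team + 2 × residual/40
- true variance: V = V₀ + 2 × school
- coverage = 2Φ(1.96 × sqrt(V₀/V)) − 1

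Example, school 0.05 and team 0.02: residual 0.93; V₀ = 0.02 + 0.0465 = 0.0665; V = 0.1665; coverage 78.5%.

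| School ICC | Team ICC 0.02 | 0.05 | 0.10 |
|---|---|---|---|
| 0.01 | 91.5% | 92.6% | 93.4% |
| 0.03 | 84.6% | 87.6% | 90.0% |
| 0.05 | 78.5% | 82.9% | 86.7% |

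**4. What the team intercept does achieve.** Simulated Type I error at nominal 5% (team ICC 0.02, 20 per team):

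| School ICC | All clustering ignored | Team intercept, Wald test | Team means, t on 2 df |
|---|---|---|---|
| 0 | 10% | 6.5% | 5% |
| 0.01 | 15% | 10% | 6% |
| 0.05 | 31% | 23% | 11% |
| 0.10 | 43% | 34% | 17% |

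**5. Team-within-school ICC.** Degrees of freedom are 4 − 2 = 2 between teams and 80 − 4 = 76 within. An observed ICC of 0.05 gives F = (1 + 19 × 0.05)/(1 − 0.05) = 2.053. The 97.5% and 2.5% points of F(2, 76) are 3.874 and 0.0253.

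- Lower: 2.053/3.874 = 0.530, and (0.530 − 1)/(0.530 + 19) = −0.02, set to 0.
- Upper: 2.053/0.0253 ≈ 81.0, and (81.0 − 1)/(81.0 + 19) = 0.80.

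The design effect 1 + 19 × ICC then runs from 1 to about 16.

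**The case against.** The protocol is candid about its limits: quasi-experimental, not powered for confirmation, estimation-focused, fragile with two clusters. Against that background, three stronger readings are tempting and the documents do not support them.

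- **That every between-arm interval is undefined.** The first three research questions concern patterns of change, which the condition-by-time term addresses, and that interval is computable. Stable school differences largely drop out of change, and baseline adjustment works in the same direction. The coverage figures above therefore apply to differences in level, not to change. For change, the problem is the omitted school-by-time variation, which these data cannot measure.
- **That the mitigation sentence is wholly false.** It speaks of clustering being ignored and hedges its claim. The team intercept does lower Type I error, for example from 31% to 23% at a school ICC of 0.05. The sentence fails for school-level clustering only.
- **That the protocol promises a school-level ICC, or plans the next trial on its own ICCs alone.** No section names a school-level ICC, and Section 2.3 already brings in published values.

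These points narrow the concern. They do not remove it, because the 95% CIs, ICCs and design effects are the emphasised outputs, and labelling a study exploratory does not identify a variance.

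**Conclusion.** The point holds in this form. The school intercept in Section 2.9 is not identifiable; this is exact and rests only on one school per arm. The CI for a between-arm difference in level depends on an arbitrary school variance, and no school-level ICC can be obtained. The condition-by-time CI is computable but carries no cluster penalty, and any school-by-time difference is fully confounded with ThriveNudge. A team-within-school ICC is estimable on 2 df, too few for useful planning by itself.

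The size of the undercoverage is conditional. It assumes that school variance is taken as zero, 20 athletes per team, and school and team ICCs that the protocol does not supply. The direction does not depend on those values as long as schools differ at all.

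The team-level randomisation wording in the Abstract and Section 3 contradicts Sections 2.1 and 2.4. Section 3's version matters most, because it describes a design in which this confounding would not arise.

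**What to change.** 1. **Section 2.9.** Delete the school random intercept. Base between-arm intervals on the four team means, or team changes, with 2 df (t = 4.30). Label them as a difference between two schools, one of which used ThriveNudge, and note that they still omit school-level variation.
2. **Section 3.** Replace the mitigation sentence with a statement that condition is fully confounded with school and that no model can separate them.
3. **Abstract and Section 3.** Correct the team-level randomisation wording to agree with Sections 2.1 and 2.4.
4. **Sections 2.3 and 4.** State that only a team-within-school ICC is estimable, report it with its 2-df interval, and say that planning at school level will rest on the published ICCs that Section 2.3 already mentions.

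The cost is revised wording and a simpler model, with no added participants. The intervals become wider.
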